### Sample size calculation

2.6.

The sample size was calculated based on the primary outcome. According to previous studies, the incidence of severe postoperative pain in patients undergoing TKA with multimodal analgesia is 25–40% (16, 17). Considering variance in multimodal analgesia and follow-up times, we reviewed the records of 20 patients who had undergone unilateral TKA in the past month. With multimodal analgesia, 48% of patients reported severe pain (NRS ≥ 7 points) within 12 postoperative hours. Therefore, we assumed that the incidence of rebound pain in patients undergoing TKA in the context of multimodal analgesia is 45%. We expect that the incidence of rebound pain in the esketamine group will be at least 35% lower than in the placebo group during the first 12 post-surgical hours. Using Power Analysis and Sample Size version 15.0 (Stata Corp. LP, College Station, TX, United States) and assuming a significance (*α*) level = 0.05 and power (1 − *β*) = 80% determined sample sizes for the esketamine group (*N*_1_) = 160 and placebo group (*N*_2_) = 160. Considering potential withdrawal (10%), a final 356 patients (178 in each group) will be included to achieve the appropriate power to test our hypothesis.

### Randomization and allocation concealment

2.7.

Participants will be assigned a study number (1–178) in order of their enrollment. We will use block randomization to assign participants to groups at a 1:1 ratio with a block length of 4. Statistical Package for Social Sciences (SPSS) version 25.0 will be used to generate and record a random number series from 1 to 6, and then arrange the blocks accordingly. Randomized allocation will be performed by the clinical trial center, which will not be involved in other aspects of the trial. The randomization protocol will be placed in a sealed, opaque envelope, and the quality controller ([name]) will open the envelope in order of grouping to determine each participant’s assignment.

### Double blinding

2.8.

This study will follow a double-blind design. According to the allocation protocol, participants will be randomized to receive a continuous infusion of esketamine or 0.9% normal saline during the operation. To ensure investigator blinding, the drug administrator ([name]) will prepare syringes (Weigao Group Medical Polymer Products Co., Ltd., Weihai, Shandong, China) in a separate room, labeling them A or B. One syringe will be filled with 50 mg of esketamine and 0.9% of normal saline (20 ml total) and the other will be filled with the same volume of 0.9% normal saline. The appearances of syringes A and B will be identical, other than label. The drug administrator will be unaware of the distribution plan and the intervention measures accepted by the participants. Because esketamine has sedative and hypnotic effects, to prevent unblinding the investigators and participants, all participants will be given preoperative 0.05 mg/kg intravenous midazolam. Throughout data collection, nurses, surgeons, outcome assessors, and statistical analysts will all be unaware of participant treatment group assignments. An independent data and safety supervision committee will monitor the trial, without disclosing participant grouping, until completion of statistical analyzes.

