### Design and setting

2.1.

This single-center, prospective, double-blind, randomized, placebo-controlled trial will be conducted at the West Coast Hospital of the Affiliated Hospital of Qingdao University. Eligible patients will be randomly assigned to the esketamine or placebo group at a 1:1 ratio (Figure 1).

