### Strategies to improve intervention adherence

2.13.

At the recruitment and screening stage, the investigator will describe the study purpose, drug intervention, research protocol, trial process, drug delivery plan (including dose, delivery method, and time period), clinical assessments, sampling frequency, biological sample collection, potential risks and benefits of participation, and compensation, to ensure each participant is fully informed before they volunteer, and to enhance participant adherence. Before the participant begins the trial, the anesthesiologist, quality controller, and drug administrator will carefully check their participant number, randomization group, dosage, and pump speed. After the intervention, these investigators will carefully count the remaining research drugs, empty packages, and drug delivery devices.

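### Two-letter syringe labels, group checks by the anesthesiologist and drug administrator, and a fixed block of 4 leave the blinding weaker than it need be

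*Protocol article*

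**What the plan says.** - **Labels.** Under Double blinding (2.8), the drug administrator prepares the syringes in a separate room, "labeling them A or B". One holds diluted esketamine and the other the same volume of saline. The section adds: "The appearances of syringes A and B will be identical, other than label". It describes no other code.
- **Who is kept blind.** The same section says that the drug administrator knows neither the distribution plan nor what participants receive. It lists nurses, surgeons, outcome assessors and analysts as unaware of group. Midazolam for all is meant to stop esketamine's sedative effect from unblinding investigators and participants.
- **Who checks the group.** Strategies to improve intervention adherence (2.13) says that "the anesthesiologist, quality controller, and drug administrator will carefully check their participant number, randomization group, dosage, and pump speed". It refers to these three roles as investigators.
- **Allocation.** Randomization and allocation concealment (2.7) says: "We will use block randomization to assign participants to groups at a 1:1 ratio with a block length of 4". The clinical trial center, otherwise uninvolved, performs the allocation. The quality controller opens sealed opaque envelopes in order.
- **Scale.** There is one center (2.1), no stratification is described, and "a final 356 patients (178 in each group) will be included" (2.6).

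**The concern.** A code with two values shared by all participants has a single point of failure: learning one participant's drug gives the meaning of the letter. With participant-specific codes, the same event reveals one person.

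The protocol article puts the group in front of two roles for whom this matters. The anesthesiologist checks it and, under Standard analgesia procedure (2.14), gives PACU rescue when the pain score calls for it. The drug administrator checks it after filling and labeling the syringes.

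The primary outcome rests on self-reported pain scores in the first 12 postoperative hours, so it is sensitive to the expectations and conduct of the people around the participant. A visible run of letters in fixed blocks of 4 also lets an observer infer some letters before they are assigned.

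**Working it through.** **1. The sections on the drug administrator, side by side.**
- 2.8: this role fills and labels the syringes, so it knows the content behind each letter. It is also said not to know what participants receive.
- 2.13: this role checks each participant's number together with the randomization group.
- If the group is shown as a letter, the role can translate it. If it is shown as a drug name, no translation is needed. Either way, the statement in 2.8 cannot hold alongside 2.13.

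The anesthesiologist does not appear in 2.8's list of blinded roles, so there is no direct contradiction there. But 2.8 aims to blind investigators, and 2.13 counts the anesthesiologist among them.

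**2. Reach of one decoding.** With A and B constant, a person who decodes one label decodes every participant whose label they know. The limit is 356, for someone who knows every label. With participant-specific codes it is 1.

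**3. The plan's own block figure.** A 1:1 block of 4 has C(4,2) = 6 patterns. This matches the plan's statement that SPSS will "generate and record a random number series from 1 to 6, and then arrange the blocks accordingly". The number of blocks is 356/4 = 89.

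**4. Labels that are certain before assignment.** A label is certain once one letter has been used twice in the block.

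| Pattern | Certain positions | Count |
|---|---|---|
| AABB, BBAA | 3 and 4 | 2 each |
| ABAB, ABBA, BABA, BAAB | 4 | 1 each |

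Expected number per block = (2×2 + 4×1)/6 = 8/6 = 1.333. As a share, 1.333/4 = 33.3%. Over the trial, 89 × 1.333 = 118.7, or about 119 of 356.

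Check by position: position 4 is always certain and position 3 is certain in 2/6 = 1/3 of blocks, so (1/4)(1) + (1/4)(1/3) = 1/3.

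**5. Best guess over all positions.** Guessing the letter used less often so far is right with probability 1/2, 2/3, 2/3 and 1 at positions 1 to 4. The mean is (1/2 + 2/3 + 2/3 + 1)/4 = 70.8%, against 50% by chance.

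**6. Longer fixed blocks, same method.** Length 6 gives 25% (356 × 0.25 = 89). Length 8 gives 20% (356 × 0.20 = 71). Length alone helps only moderately. The larger gain comes from removing the visible letters.

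**The case against.** The strongest reply is that the article never says A and B mean the same thing for everyone. Its wording could also describe a pair made up for each case, with the assignment opened separately, and a condensed article may leave code handling to the full protocol. This stands as a limit: a constant code is implied, not documented. A reader might infer that one unmasking certainly exposes the whole trial; the text supports that only conditionally, and only for people who know the labels.

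Other stronger readings also fail:
- **One-third prediction.** It needs knowledge of every earlier label in the block and of where blocks start. The uninvolved trial center and the sealed envelopes protect the next assignment directly. They do not prevent inference from labels already seen.
- **Biased enrolment.** Knowing that the next letter is A gives no reason to select a patient unless A has been decoded. Both leaks must reach the same person.
- **Serious adverse event reports as a leak.** Adverse event reporting (3.5) describes notification and recording, and nothing there discloses allocation.
- **Biased diary coaching.** Diary training takes place the day before surgery (2.9), before any drug effect can be seen.
- **A recognized drug reaction.** This is a guess, not a decoding. Everyone receives midazolam, and 2.12 expects the dose not to cause dissociative effects.
- **Ward exposure.** The infusion ends at knee suture, and no section places the labeled syringe on the ward. The documented exposure is at the group check and, through the anesthesiologist role, in the PACU.

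Finally, unique labels would make the block length matter much less. That is correct, so the block change is secondary.

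**Conclusion.** The point holds as a weakness in a stated procedure that is cheap to correct. It is not evidence that the blind will be broken.

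- **Shared code:** if A and B keep one meaning, one decoding reaches every participant whose label the decoder knows, instead of one participant. The constant meaning is an assumption that the text suggests.
- **Conflict between sections:** 2.8 and 2.13 disagree on what the drug administrator may know. This does not depend on the constant meaning.
- **Block length:** an expected one third of labels, about 119 of 356, is certain for a fully informed observer, and less for anyone who knows less. It threatens enrolment only together with a decoded letter.

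The documented safeguards lower these risks without closing the routes. The sample size and the planned analysis are not affected.

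**What to change.** 1. Replace the A/B labels with the participant's unique study number and nothing else. The clinical trial center holds the key, and any code break is made for one participant at a time. The numbers must be unique across all 356 participants; section 2.7 gives the range as 1 to 178, which is too short for that.
2. Reconcile 2.8 and 2.13: state which roles may see the group and in what form, and limit the pre-infusion check for all other roles to the study number and pump settings. Correct the statement about the drug administrator accordingly.
3. As a secondary safeguard, use varied block sizes (for example 4, 6 and 8) and do not disclose them to recruiting or treating staff.

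**Cost:** a new list and label template. If recruitment stops mid-block, the arms can differ by at most half the last block: 4 participants for a block of 8, against 2 for a block of 4.

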### Self-reported pain scores

2.9.

Rebound pain will be defined based on self-reported pain score. The participant’s pain score will be recorded in a pain diary prepared by the clinical trial center. An investigator ([name]) will train the participants to use the pain diary and patient-controlled intravenous analgesia (PCIA) device 1 day before their operation. The pain diary consists of three parts: first, basic participant information (e.g., name, age, sex, height, weight, complications); second, operation and anesthesia information (e.g., surgical procedure, anesthesia procedure, postoperative analgesia mode, prescription analgesics, related analgesia pump parameters); third, the NRS and recording times. The anesthesiologist will complete the first and second parts during the operation; the participant will complete the third part.

The pain diary stipulates that when the participant first experiences postoperative pain, they must accurately rate their pain severity and record the rating time using the pain face scale and ruler. The ward nursing staff will judge whether to start remedial analgesia according to the participant’s pain score. If the participant does not need remedial analgesia when the first pain occurs, they will also record their highest degree of pain during the first pain buffer period. The pain buffer period is defined as the time elapsed from tolerable pain (NRS < 4) to needing analgesic rescue intervention (NRS ≥ 4). If the participant has received remedial analgesia, they will record their highest degree of pain during the first pain cycle. The pain cycle is defined as the time elapsed from the pain requiring analgesic rescue intervention to when the pain is tolerable (NRS < 4). For each pain or buffer cycle, the participant will report their highest NRS and each cycle’s start and end time, until 24-h postoperative. The type, dose, and time of remedy analgesics given by the nursing staff will need to be accurately recorded in the pain diary (Figure 2).

**Figure 2 fig2:**
[figure not shown]
Participants report pain scores using a pain diary.

### Ultrasound-guided adductor tube block procedure

2.10.

Before anesthesia, each participant will receive an ultrasound-guided adductor tube block in the nerve block room. Their peripheral venous access will be opened, and they will undergo three-lead electrocardiography (ECG), noninvasive blood pressure, and blood oxygen saturation monitoring. The participant will be placed supine, and the inner thigh of the affected side will be turned outward for full exposure. Polyvinylidene disinfectant (Nanjing Zhonghe Pharmaceutical Co., Ltd., Xuzhou, Jiangsu, China) will be used for skin disinfection. Sterile protective cover (Puen, Yangzhou Yutuo Medical Instrument Co., Ltd., Yangzhou, Jiangsu, China) will be used to cover high-frequency linear array probes (8–14 MHz). First, the anesthesiologist will place the probe at the anteromedial end of the middle thigh to find the short-axis section of the femoral artery. When the probe is positioned correctly, the skin, subcutaneous tissue, sartorius muscle, medial femoral muscle, and adductor magnus can be seen under ultrasound. At this position, the femoral artery, vein, and saphenous nerve will be located in the space surrounded by three muscles (Figure 3A). The anesthesiologist will use the in-plane technique to inject the needle from the outside to the inside toward the femoral artery. The needle tip target position is between the sartorius muscle, medial femoral muscle, and anterolateral side of the femoral artery. After the puncture needle breaks through the adductor femoris muscle membrane and its tip reaches the target position and no blood is drawn back, 1 ~ 2 ml of normal saline will be injected to confirm the diffusion position, after which 20 ml of 0.375% ropivacaine (AstraZeneca Pharmaceutical Co., Ltd., Wuxi, Jiangsu, China) will be injected. The sign of a successful block is that under ultrasound, the injected liquid can be seen surrounding the artery and spreading in the adductor tube like an ellipse (Figure 3B). Twenty 20 min after the block, the participant will be transferred to the operating room.

**Figure 3 fig3:**
[figure not shown]
**(A)** The target for ultrasound-guided adductor canal block; **(B)** Diffusion of local anesthetic drugs within the adductor canal. 1, Femoral artery; 2, Sartorius muscle; 3, Medial vastus muscle; 4, Adductor magnus; 5, Saphenous nerve.

### Spinal anesthesia procedure

2.11.

After completing the adductor tube block, the participant will be placed in a lateral recumbent position (surgical side downward). The back of their spine will be close to the edge of the operating table and perpendicular to the ground. Their head will be bent forward and cushioned with a high pillow, their back curved, and their knees held with both hands. The anesthesiologist will locate the intersection between the line of the highest point of the posterior superior iliac spine and the spine: the fourth lumbar spine process (L_4 ~ 5_ space). The common puncture points are the L_3 ~ 4_ or L_2 ~ 3_ space. The anesthesiologist will choose the direct or lateral approach. The direct approach requires local infiltration anesthesia at the midpoint of the puncture space. The left thumb is fixed on the skin, and the right hand holds the No. 9 subarachnoid puncture needle (Henan Tuoren Medical Equipment Group Co., Ltd., Changheng, Henan, China). After passing through the skin, subcutaneous tissue, and supraspinous and interspinous ligaments, the needle is inserted with both hands. Resistance increases when the needle meets the ligamentum flavum. Cerebrospinal fluid outflow from the aspiration core confirms entry into the subarachnoid space. The puncture point for the side entry method should be 0.5 cm from the central line, and the puncture needle should be inclined 15° to the central line, with other procedures the same as the direct entry method. After confirming the free flow of cerebrospinal fluid through the needle, 10–15 mg of heavy gravity ropivacaine are administered. Post-injection, the participant will maintain the lateral position for 3–5 min, then turn and lie supine. The anesthesiologist will check for sensory changes and disappearance area, adjusting the participant’s body position as appropriate.

### Interventions

2.12.

Placebo group participants will receive an intravenous infusion of 0.9% normal saline (Weigao Group Co., Ltd., Weihai, Shandong, China). The infusion pump (Henan Tuoren Medical Equipment Group Co., Ltd., Changheng, Henan, China) mode is constant speed pumping, and the pumping time is from the end of the intraspinal anesthesia administration to the knee joint suture. The anesthesiologist can choose the appropriate medication protocol according to clinical practice, but other NMDA receptor antagonists, such as dextromethorphan and amantadine, will not be used.

Esketamine group participants will receive an intravenous infusion of esketamine (Jiangsu Heng Rui Medicine Co., Ltd., Jiangsu, China) following a standard dilution protocol [2 ml (50 mg) esketamine with 0.9% normal saline to 20 ml, 2.5 mg/ml]. The infusion rate of esketamine is 0.3 mg/kg/h, the mode of the infusion pump is constant speed pumping, and the infusion time is from the end of the spinal anesthesia administration to the knee joint suture. Drug managers need to monitor that the maximum dose of esketamine is not more than 0.5 mg/kg.

The esketamine dose selection was based on published clinical trials and drug manufacturer instructions. Koppert et al. (18) selected 13 healthy adult men to establish a pain model by inducing persistent pain and secondary mechanical hyperalgesia via transcutaneous electrical stimulation. In the trial group, 0.3 mg/kg/h esketamine was continuously infused for 30 min, and the observation index was the area of persistent pain, punctate hyperalgesia, and abnormal pain. The size of punctate hyperalgesia was significantly reduced and did not affect the hyperalgesia area. All participants felt comfortable after the procedure, quickly answered the investigators’ questions, and no anesthesia emergence was observed. For select major laparotomies (colorectal and liver surgeries), Bornemann-Cimenti et al. (14) formulated two drug delivery protocols: low-dose esketamine (no initial dose, followed by continuous infusion of 0.015 mg/kg/h for 48 h) and conventional low-dose esketamine (initial dose of 0.25 mg/kg, followed by continuous infusion of 0.125 mg/kg/h). The outcome indicators were opioid consumption, hyperalgesia, and postoperative delirium. Both protocols reduced postoperative opioid use and hyperalgesia, but the conventional low-dose group was more prone to delirium compared with the low-dose group. Trimmel et al. (19) showed that low-dose esketamine 0.125–0.25 mg/kg could produce analgesic effects with minimal incidence of adverse mental reactions. Nevertheless, adverse mental reactions can be as high as 12% at high doses. When the dose is increased to 0.5 ~ 1.0 mg/kg, separate anesthesia and adverse reactions increase accordingly. Increasing evidence suggests that esketamine should be used as an analgesic in adults to reduce postoperative opioid use. While esketamine doses were inconsistent in these studies, continuous perioperative infusion seems to be most effective for controlling postoperative pain.

TKA surgery in our center is expected to last 1–1.5 h. Due to the controlled use of psychotropic drugs, we plan to administer esketamine by continuous infusion at 0.3 mg/kg/h during surgery. This dose is lower than the specified dose in the manual and has analgesic and anti-hyperalgesia effects without causing adverse reactions like separation anesthesia. To ensure investigator and participant blinding and reduce mental symptoms, all participants will receive midazolam 0.05 mg/kg after spinal anesthesia. Before the operation, all participants will receive 0.5 mg of phenazopyridine hydrochloride (Chengdu List Pharmaceutical Co., Ltd., Chengdu, Sichuan, China) to antagonize the effect of esketamine on the M-cholinergic receptor.

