### Safety outcomes

3.3.

(1) nausea and vomiting; (2) respiratory depression (i.e., blood oxygen saturation < 93%); (3) hypertension (i.e., blood pressure > 30% of baseline value); (4) hypotension (i.e., blood pressure < 30% of baseline value); (5) tachycardia (i.e., heart rate > 100 beats/min); (6) bradycardia (i.e., heart rate < 50 beats/min); (7) nervous system complications (restlessness, delirium, nightmare, restlessness); (8)increased secretions; (9) nerve injury caused by regional block or local anesthetic poisoning; (10) wound infection, deep vein thrombosis, or pulmonary embolism.

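### The dose rationale says flatly that the dose does not cause dissociation, which the protocol's own figures do not support, and dissociation is not a named safety outcome

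*Protocol article*

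**What the plan says.** All dosing text is in the protocol article, section 2.12 (Interventions).

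- **Regimen.** "The infusion rate of esketamine is 0.3 mg/kg/h, the mode of the infusion pump is constant speed pumping". It starts once the spinal drug has been given and stops when the knee is sutured. The total may not exceed 0.5 mg/kg. On duration: "TKA surgery in our center is expected to last 1–1.5 h".
- **Evidence cited for this rate.** A study of 13 healthy men: "In the trial group, 0.3 mg/kg/h esketamine was continuously infused for 30 min".
- **Dose ranges cited for mental effects.** At the lower end, "low-dose esketamine 0.125–0.25 mg/kg could produce analgesic effects with minimal incidence of adverse mental reactions". Higher up, "When the dose is increased to 0.5 ~ 1.0 mg/kg, separate anesthesia and adverse reactions increase accordingly".
- **Conclusion drawn.** The dose "has analgesic and anti-hyperalgesia effects without causing adverse reactions like separation anesthesia". The same paragraph says the dose is below that in the product manual, and gives every participant midazolam, partly to lessen mental symptoms.

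Section 3.3 (Safety outcomes), item (7), reads "nervous system complications (restlessness, delirium, nightmare, restlessness". Section 3.5 defines an adverse event as any untoward symptom, sign or test result, whether reported by the participant or found by inquiry or examination.

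**The concern.** The conclusion is worded without qualification, yet the tolerability evidence cited for this rate comes from an infusion much shorter than the planned one. The rate matches, but the total does not. On the section's own ranges, the planned total lies above the one linked to few mental reactions, and the cap touches the one where dissociation is said to rise. (I read separation or separate anesthesia as a rendering of dissociative anaesthesia.)

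Dissociation is also the reaction that the dose rationale singles out as dose-related, but the printed safety list does not name it, while another term in that item appears twice. The trial could report no difference in nervous system complications without having asked every participant about the effect that its rationale says will not occur. What is at stake is the safety conclusion and the dose rationale. The primary outcome and its analysis are unaffected.

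**Working it through.** The plan states no total dose, so there is no figure of its own to reproduce. The total follows from the stated rate and duration.

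**Inputs (all section 2.12):** rate 0.3 mg/kg/h, constant; expected surgery 1–1.5 h, used as a proxy for infusion time; cap 0.5 mg/kg; volunteer study 0.3 mg/kg/h for 0.5 h; range linked to few mental reactions 0.125–0.25 mg/kg; range linked to more dissociation 0.5–1.0 mg/kg.

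**Step 1. Total dose = rate × time.**
- Volunteer study: 0.3 × 0.5 = 0.15 mg/kg
- Trial, 1 h: 0.3 × 1 = 0.30 mg/kg
- Trial, 1.5 h: 0.3 × 1.5 = 0.45 mg/kg

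**Step 2. Planned total against the cited totals.**
- Against the volunteer study: 0.30/0.15 = 2 and 0.45/0.15 = 3
- Against the top of the lower range: 0.30/0.25 = 1.2 and 0.45/0.25 = 1.8
- Against the bottom of the upper range: 0.30 and 0.45 are both below 0.5

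**Step 3. Time to reach each boundary = dose / rate.**
- 0.25 mg/kg: 0.25/0.3 h = 50 min, before the shortest expected operation ends
- 0.5 mg/kg: 0.5/0.3 h = 100 min, 10 min beyond the longest expected operation

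The expected total therefore falls in the gap between the two cited ranges, on which the section is silent. Only the cap meets the upper range, and only at its lowest point.

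**Step 4. Safety list against the rationale.** Item (7) has three distinct terms: restlessness (twice), delirium and nightmare. Neither dissociation nor hallucination appears there or elsewhere in section 3.3. Section 3.5 would record dissociation if it were volunteered or found, but does not require that every participant be asked. Section 7 analyses the safety outcomes in a safety dataset, so what section 3.3 names determines what is compared.

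**The case against.** **The two statements are compatible on dissociation.** The section places the rise in dissociation at 0.5–1.0 mg/kg, and the expected total is below that. The lower range concerns mental reactions generally and is not offered as a limit for avoiding dissociation. The cap is a ceiling, not the planned dose. This stands: a reader might infer that the protocol refutes itself, and it does not. It makes an absolute statement where its evidence is silent.

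**Cumulative mg/kg may be the wrong measure.** The cited ranges carry no mode of administration, and a slow infusion may give lower peak levels than the same dose given quickly. This stands as a limit on the ratios. The protocol does not make that argument, however, and its own cap is a total in mg/kg.

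**The protocol does not treat the drug as free of mental effects.** It refers to the product manual, which is not shown, caps the total, gives midazolam to everyone, and in section 3.4 mentions procedures for psychiatric symptoms. This is fair, but it is a reason to soften the sentence.

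**Adverse event reporting would catch dissociation.** It could, and the CRF, which is not shown, may prompt for it. The repeated word may also be a translation slip hiding a different term. Even so, the article prints the list, and the list is faulty as printed.

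**Two further inferences should not be drawn.**
- A reader might set the trial beside the cited laparotomy regimen that had more delirium (0.25 mg/kg, then 0.125 mg/kg/h) by cutting that regimen to 1–1.5 h. Its duration is not stated; the only duration given is 48 h, for the other arm. That arm totalled 0.015 × 48 = 0.72 mg/kg, above this trial's cap, and had less delirium, so totals do not compare simply across infusions of such different length.
- A reader might infer that participants are being misinformed. The consent text is not shown, and sections 2.2 and 3.4 require side effects and risks to be explained.

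**Conclusion.** The point holds in a limited form. The flat statement that the dose does not cause dissociation is unsupported by the protocol's own figures: the expected total of 0.30–0.45 mg/kg is 2–3 times the exposure in the volunteer study cited for the rate and 1.2–1.8 times the top of the range linked to few mental reactions. The direct tension is confined to the cap of 0.5 mg/kg, reached only if the infusion lasts 100 min.

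This rests on two assumptions: that cumulative mg/kg is the relevant measure, and that operating time approximates infusion time. The infusion runs from the spinal injection to suture, so the true total may be somewhat higher or lower.

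Separately, and without either assumption, section 3.3 item (7) repeats one term and does not name dissociation. The document therefore fixes no systematic, prespecified comparison of the reaction that its rationale singles out. It does not follow that dissociation would go unrecorded, only that its recording would depend on report or inquiry.

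**What to change.** 1. In section 2.12, state the planned total dose over the expected duration, with the existing cap, beside the totals of the cited studies, and reconcile these passages. Remove the absolute statement, or limit it to what the cited evidence covers. No change of dose is proposed here.
2. In section 3.3 item (7), replace the repeated restlessness with dissociation/hallucination. If the repeat stands for some other intended term, restore that term as well.
3. Have the blinded assessor ask every participant about it at the PACU visit and on the first postoperative day, both already in Table 1, and compare the arms in the safety analysis.

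**Cost:** protocol wording, one or two CRF questions at scheduled visits, a slightly longer PACU assessment, and a less favourable safety statement in the rationale. The sample size and primary analysis do not change.
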